### **Calculation for the variance of the population size estimate and standard errors using the multiplier method**

Using the following formula derived from the Delta method we can calculate the variance of the population size estimate and 95% confidence bounds around our estimate:

$$V(S) \approx (n_2^2) * (1 - (n_2/m)) / (m * ((n_2/m)^3)) + (r^2) * n_1$$

where V(S) is the variance of the population size estimate; n1 the number of MSM receiving a unique objects from data source 1; n2 is the total number of sex workers, MSM or transgender women interviewed in the RDS; m is the number of sex workers, MSM or transgender women interviewed in the RDS receiving a unique object; r is the ratio of m to n2.

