### **E. Sample Size**

The sample size will be calculated based on the budget and the estimated number of sex workers, men who have sex with men and transgender women that are thought to be reachable (Table 3). For PLACE/Programmatic mapping the exact number of each population interviewed will depend on the site identification, verification and patron and worker interview steps.

Approximately 2000 men and women will be interviewed and tested for HIV at venues in Luanda. We expect to recruit approximately 600 sex workers, 600 men who have sex with men and 200 transgender women. Around 600 participants could be from the general population. Approximately 400 female sex workers will be recruited in Cabinda using RDS.

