### ***RDS Population Size Procedures***

We will use the unique object multiplier method to obtain a population size estimate of female sex workers in the province of Cabinda. The multiplier method is the most commonly used population size estimation method, in part because it is relatively straightforward and utilizes simple calculations. The unique object multiplier method involves the distribution of a set number of unique objects, such as key chains, to members of the target population. Unique objects will be distributed widely at specific locations where female sex workers congregate (i.e. bars, brothels, hotels, etc.). The goal is to distribute as many unique objects as possible, but no less than the agreed upon study sample size.

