## **VIII. Data Analysis**

### ***A. RDS Analysis***

RDS-based surveys will be analyzed with RDSAT or RDS-A, free software packages that adjust RDS-collected data for network sizes and recruitment patterns. Using RDSAT and NetDraw, a software for drawing social

networks, we will examine the equilibrium of key variables and recruitment patterns by key demographic characteristics to identify potential biases associated with recruitment (i.e. homophily, number of recruitment chains). We will exclude all data from seeds in the analysis and export RDSAT weights directly into SAS to conduct analyses not supported by RDSAT. We will also use RDSAT to generate population estimates for specific key indicators from UNAIDS and PEPFAR^2 for behavioral surveillance purposes (Table 4).

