**The formula for estimating the population size using a multiplier is**

$$N = \frac{(n_1 \times n_2)}{m}$$

where N is the estimate of total population size; n1 is the number of individuals receiving unique objects; n2 is the number of individuals participating in the RDS; m is the number in both populations (i.e. the number of MSM who received unique objects and participated in the RDS)

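### The variance formula for the unique-object size estimate is not the delta-method variance of N = n1·n2/m: it is negative at low overlap and wrong in either direction elsewhere

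*Protocol*

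**What the plan says.** Section VIII.C, under the multiplier formula, sets N = n1·n2/m, where n1 is the number of people given an object and "n2 is the number of individuals participating in the RDS". The next subsection, on the variance and standard errors, says the variance comes from the delta method and will supply 95% confidence bounds. After its opening bracket the expression reads "n_2^2) * (1 - (n_2/m)) / (m * ((n_2/m)^3)) + (r^2) * n_1".

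The symbols are defined in the same place. As before, n2 counts everyone surveyed through RDS. The overlap count is given by "m is the number of sex workers, MSM or transgender women interviewed in the RDS receiving a unique object", which makes it a part of n2. The remaining symbol is the overlap proportion itself, since the subsection states that "r is the ratio of m to n2".

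On the inputs, Section VI.E says "Approximately 400 female sex workers will be recruited in Cabinda using RDS". Section VI.F, RDS Population Size Procedures, says of the objects: "The goal is to distribute as many unique objects as possible, but no less than the agreed upon study sample size". The Sample Size paragraph in that section adds that distribution should saturate the target population. It gives no expected overlap. Section VIII.A says the RDS software will "adjust RDS-collected data for network sizes and recruitment patterns" and that seeds are excluded from the analysis.

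**The concern.** People counted in m are among those counted in n2, so n2/m cannot be below 1 and the factor (1 − n2/m) cannot be positive. A variance whose sampling term is never positive cannot be right. That term also contains no n1, although N is proportional to n1, so its spread must scale with n1.

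The size of this population is a stated objective of the Cabinda survey (Section V), and Section VIII.C intends size estimates as coverage denominators and as input to epidemic projections. At stake is the uncertainty reported around that figure. Where the formula is negative there are no bounds to report. Where it is positive the analyst gets a number that looks usable and is wrong, and nothing warns of it.

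**Working it through.** The protocol states no numeric variance, standard error or interval, so there is no figure to reproduce. The check evaluates the formula with its own definitions.

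**Inputs.** From the documents: n2 about 400 (slightly fewer once seeds are excluded) and n1 at least 400. Assumed: n1 above 400, and every value of m. All results are for simple random sampling, with no RDS design effect.

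**Step 1: simplify the printed formula.** Put p = m/n2, so m = n2·p and n2/m = 1/p.
- First term: n2²·(1 − 1/p) / (n2·p·p⁻³) = n2·p²·(1 − 1/p) = −n2·p(1−p).
- Second term: r²·n1 = n1·p².
- Sum: V = n1·p² − n2·p(1−p).

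**Step 2: when it is negative.** V < 0 when n1·p < n2·(1−p), that is p < n2/(n1+n2), or equivalently N > n1(n1+n2)/n2. With n2 = 400:

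| n1 | V negative when p is below | equivalently N above |
|---|---|---|
| 400 | 0.50 | 800 |
| 600 | 0.40 | 1,500 |
| 800 | 0.33 | 2,400 |
| 1,200 | 0.25 | 4,800 |

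**Step 3: the delta-method variance.** N = n1/p, so dN/dp = −n1/p² and V(N) = n1²·V(p)/p⁴. With binomial V(p) = p(1−p)/n2 this is n1²(1−p)/(n2·p³). If n1 is treated as a Poisson count, add n1/p². A binomial simulation with n1 fixed (200,000 draws per setting) agrees: 62 against 61 at n1 = 400, p = 0.4; 81 against 80 at n1 = 800, p = 0.5; 12.6 against 12.5 at n1 = 400, p = 0.8.

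**Step 4: compare.**
- n1 = 400, m = 100 (p = 0.25, N = 1,600). Printed V = 25 − 75 = −50. Correct V = 160,000 × 0.75 / (400 × 0.015625) = 19,200, SE 139; with the Poisson term, 19,200 + 6,400 = 25,600, SE 160.
- n1 = 800, m = 200 (p = 0.5, N = 1,600). Printed V = 200 − 100 = 100, SE 10. Correct V = 640,000 × 0.5 / (400 × 0.125) = 6,400, SE 80; with the Poisson term, 9,600, SE 98. The 95% half-width would be about 20 (1.96 × 10) instead of about 157 (1.96 × 80).
- n1 = 400, m = 360 (p = 0.9, N = 444). Printed V = 324 − 36 = 288, SE 17.0. Correct V = 160,000 × 0.1 / (400 × 0.729) = 54.9, SE 7.4; with the Poisson term, 54.9 + 493.8 = 548.7, SE 23.4.

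**Step 5: try the obvious repairs** at n1 = 400, p = 0.2, where the correct SE is 200 (224 with the Poisson term).
- Inverting n2/m only: 160,000 × 0.8 / (80 × 0.008) + 16 = 200,016, SE 447.
- Swapping m and n2 throughout: 6,400 × 0.8 / (400 × 0.008) + 25 × 400 = 11,600, SE 108.

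Neither works, because several terms are wrong. The leading n2² should be n1², n2/m should be m/n2, the m in the denominator should be n2, and r is upside down in the second term.

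**The case against.** **The negative range may not be where the study lands.** A reader might infer that the variance is negative over most of the plausible range. The documents do not support that. At the minimum of 400 objects the negative region is just under half of the possible overlaps, and it shrinks as n1 rises. Section VI.F asks for as many objects as possible and aims at saturation, which pushes p up. No Cabinda population size is given. At 2,200, the Luanda female sex worker figure in Section IV.A (another province), V is −46 at n1 = 400 and −35 at n1 = 600, but +13 at 800 and +258 at 1,200. This objection stands against any claim about how often the formula fails. It does not rescue the formula.

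**The bounds are not always too narrow.** This also stands. Against the version with n1 fixed, the printed SE is already too large at n1 = 400, m = 320 (13.9 against 12.5) and clearly so at m = 360. Against the version with the Poisson term it is too small at both (27.9 and 23.4).

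**It may be a typing slip.** The same ratio appears twice, and r is defined separately in prose as m to n2. No single correction yields the right expression, and no other section repairs it.

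**The size estimate is sound.** This is correct. N = n1·n2/m is the right multiplier, and no passage carries its variance into the coverage figures. A reader might infer that the coverage denominators are wrong, but the error concerns only the uncertainty reported around the estimate.

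**RDS adjustment is already planned.** Section VIII.A commits to it, and the choice of variance method can be left to the analysis plan. What remains is that the variance subsection works from raw counts and does not refer to that analysis.

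**Conclusion.** The printed expression is not the delta-method variance of the protocol's estimator. With n2 about 400 it gives no standard error when p is below 0.5 at n1 = 400 or below 0.33 at n1 = 800. Elsewhere it can be too small by a factor of 8 (n1 = 800, m = 200, n1 fixed) or too large by a factor of about 2.3 (n1 = 400, m = 360, n1 fixed; 17.0/7.4).

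That the formula is wrong follows from the definitions alone and needs no planning assumption. The sizes rest on assumed n1 and m and on simple random sampling; a design effect above 1 would raise the correct standard errors. Higher overlap does not cure the fault. It moves the analysis to where the formula returns a positive number and the error no longer announces itself.

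**What to change.** Replace the variance expression in Section VIII.C with V(N) = n1²·V(p)/p⁴, where p is the proportion of RDS participants who received the object. State that under simple random sampling this equals n1²(1−p)/(n2·p³). If n1 is to be treated as a random count, add n1/p², written as (n2/m)²·n1; if r is kept for that term, define it as n2/m.

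Add a cross-reference so that p and V(p) come from the RDS-adjusted analysis in Section VIII.A, and use the same p in N = n1/p so that the bounds belong to the estimate reported. State whether n1 is treated as fixed or random, since this changes the interval materially at high overlap.

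The cost is one corrected formula and a sentence or two of definitions. No new data, forms or sample size are needed.

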## **Assumptions**

Members of the sex worker, MSM or transgender population must have a chance of being included in both sources of data. Data from both sources will be evaluated for any potential barriers to inclusion of members of the target population. Where this assumption is violated, this will be clearly documented and reported, and other sources of data will be considered.

The multiplier method requires clear and consistent population definitions, time reference periods, and catchment areas between the different data sources. During preparation for implementation of multiplier activities and collection of unique object and survey data, these issues will be carefully considered, and investigators will ensure that definitions across data sources will be coordinated.

**Objective 8: To provide data to inform and guide future behavioral surveys and prevention strategies targeting sex workers, MSM or transgender women in Angola.**

Responses collected at a roundtable meeting with key stakeholders held at the end of data collection will be analyzed. We will invite all USG agencies, local NGOs, and key government officials to discuss how survey results can assist ongoing and future behavioral activities targeting sex workers, MSM and transgender women and how these results can advance priorities outlined in the Country Operating Plan (COP) and Angola's National Strategic Plan (NSP). Priorities for Local AIDS Control Efforts (PLACE) studies in identifying high transmission HIV/AIDS areas to improve HIV prevention program delivery. Combined data from objectives A, B and C will be used to guide the design of new prevention messages targeting sex workers, MSM and transgender women. All results will be shared with NGOs and other agencies working directly with sex workers, MSM and transgender women in Angola.

## **IX. ETHICAL CONSIDERATIONS**

### ***A. Protocol Approval and Confidentiality Protection***

Any protocol involving human subjects must follow internationally accepted practices with assurance and confidentiality. The protocol will be submitted for local ethics approval to the INSP Ethics Committee and will be reviewed by the Institutional Review Board at the University of North Carolina. In addition to the survey protocol, the INSP ethics committee will review the content and language of the informed consent form to be sure that they can be easily understood by the survey participants and also to ensure that all aspects of this research survey are appropriately explained to the subjects prior to enrollment. In order to protect confidentiality, neither participants' names nor personal identifying information will be attached to any of the survey forms. All forms will be identified only by a unique personal numeric code. Survey records will be kept in a locked file cabinet in the main survey office at the Tchikos until completion of the project and then destroyed. All official protocol files (protocol and forms, IRB minutes and approvals) will be kept on a secure server at UNC. All consent forms will be kept at the Tchikos office and copies will be given to the participants. The database will be sent to collaborators at the UNC on a regular basis.

### ***B. Confidentiality and Data Protection***

No personal identifying information will be collected as part of this study. All datasets will not have any personal information stored; each record will be identified by a unique study ID number and participants will be assigned a unique identifier code (UIC) based on personal information such as birth year and parents given names. The UIC components will be investigated as part of the Mapping Readiness Assessment and finalized before the PLACE or RDS survey initiation.

Databases, computers and smartphones and forms will be protected. Databases will be password protected and only persons working in the study will have access. Laptop computers and study forms will be locked in filing cabinets or drawers when not being used by study staff.

All field team members will have to sign a data use and confidentiality agreement prior to the data collection phase.

### ***C. Consent Process***

Trained interviewers will obtain written informed consent from all survey participants. Interviewers will initial or mark the consent form with an 'X' to verify that the content of the informed consent was explained and that the individual voluntarily agreed to participate. Participants will be informed about their rights to stop the interview at any time and to refuse any questions they do not feel comfortable answering.

### ***D. Potential Risks to Participants***

Inconvenience to participants may occur due to the time required to complete the survey. A psychological risk due to the sensitive nature of the questions may exist. The survey will be administered through smartphone in a private setting and will not contain any personal identifiers. The risk of inadvertent disclosure of HIV or STI status to interviewers if positive also exists. Investigators are not required to report to the MOH HIV status or risk related behaviors. Participants will be told that they can refuse to answer any question they do not feel comfortable answering. Any interview in which physical injury, psychological, social or economic harm to participants is detected will be terminated immediately. Homosexuality and sex work are not effectually prosecuted in Angola/

There are minimal physical risks of bleeding, bruising, fainting or light-headedness and rare risk of infection related to needle sticks. However, the survey will hire only trained medical personnel and will ensure an adequate supply of new, sterile disposable needles. Survey participants may experience discomfort during genital exams and sample collection.

There is inconvenience to participants due to the time required to complete the survey and collect samples. There are also some psychological risks from learning that one has an STI or HIV, and the risk of inadvertent disclosure of HIV or STI status if positive. Every participant will receive pre-test and post-test counseling, preliminary HIV, syphilis and Hepatitis B and if applicable, CD4 results will be provided the same day of testing. Confirmatory results for syphilis and HIV as well as gonorrhea, chlamydia, trichomoniasis and viral load will be available in two weeks. Personnel at the clinics have been trained specifically to counsel clients regarding HIV test results. Participants found to be HIV or STI-positive will be referred to specialized care for further evaluation and treatment. Participants will be encouraged to notify their partners if they have been diagnosed with STI or HIV, this entails a risk of breakdown in relationships or other negative consequences. Strategies for

partner notification will be discussed during counseling and for HIV-positive participants, couples counseling will be offered.

### ***E. Potential Benefits to Participants***

The benefits to the participant in the survey include education, testing and treatment for sexually transmitted infections, education on STI and HIV infection and counseling to prevent HIV transmission to partners. In addition, participants' sex partners will have the opportunity to be treated, minimizing the risk for re-infection with the STI and possible adverse sequelae. Participants with asymptomatic STI will have the opportunity for diagnosis and treatment using laboratory tests, which is above and beyond standard of care in Angola.

Other benefits include referral to an HIV specialist for complete examination and treatment. The country of Angola will benefit because information on HIV and STI prevalence and the population at different stages of the HIV treatment cascade will be available. The information collected in this survey will contribute directly to the design and evaluation of interventions among the surveyed groups.

### ***F. Reimbursement for Participation***

RDS recruited participants will also receive a gift for participant and as motivation for bringing their invitees to the study site (maximum of three). These token gifts will include T-shirts, make-up, a small handbag or mobile phone credit valued at 900 Angolan Kwanzas (~9USD). Remuneration for time and cost for participant-driven recruitment provided in this study is small enough to be considered non-coercive, does not cause undue inducement, is not excessive, and does not compromise the voluntariness necessary for informed consent. If the risk of harm from recruitment or participation is identified during the interview process, study staff can choose to withhold recruitment or remuneration.

### ***G. Possible Adverse Events from Survey***

We do not anticipate any adverse events from these surveys since they are cross-sectional in nature.

Unanticipated Adverse Events (UAE) are defined as unforeseen problems involving risks to subjects or others encountered during the survey. This includes: 1) physical injury to a participant, 2) psychological, social, or economic harm to a participant, 3) breaches of protocol, such as breakdowns in the informed consent process, violations of confidentiality or data privacy of a participant, and complaints by participants or their representatives, and 4) any serious or continuing non-compliance with federal regulations by investigators or research staff. These events will be reported to the survey ethics committee and data monitoring group within 72 hours of the discovery of the adverse event. Any interview in which physical injury, psychological, social or economic harm to participants is detected will be terminated immediately.

## **X. DISSEMINATION OF FINDINGS**

The main actors in the HIV response in each province will be invited to participate in a workshop presentation of the results and hence the priority action plan based on the sites / people at risk identified. The workshops will be by region. The dissemination/data use workshops have the objective to translate evidence into service delivery planning and action.

UNC, FHI 360 and Tchikos will establish and strengthen community committees as well as strengthen the capacity of peer educators and case managers to collect, analyze and use routine M&E data with a view to quarterly stakeholder data review meetings in year two. Towards this end, the study team will develop tools for provide training/technical assistance on data interpretation and use for planning. Community committees will consist of key population community groups and networks that will serve as a mechanism for communities to provide feedback and to shape quality of program services.

Data collected from this study will be disseminated to different audiences at different times. A final report will be presented to the INLS and USAID. At the end of the study, a seminar presenting significant findings will be organized in Luanda and presented to all stakeholders, including civil society.

The results will also be disseminated to the scientific community through peer-reviewed publications and presentations at national and international scientific conferences. All data will need pre-approval from the UNC prior to dissemination.

UNAIDS. Monitoring the Declaration of Commitment on HIV/AIDS: Guidelines on Construction of Core Indicators: 2008 reporting. Switzerland: WHO. 1-144.

PEPFAR. Next Generational Indicators Reference Guide. Version 1.1. Washington DC, 2009. Accessed on December 8, 2009 at <http://www.pepfar.gov/documents/organization/81097.pdf>

## XI. CHRONOGRAM

Survey preparation activities began in May 2015 and field work and interviews are scheduled to begin in September 2015. It is anticipated that data collection, analysis, and dissemination will be finalized in June 2016.

| Activity                                                 | August |  |  | September |  |  | October |  |  | November |  |  | December |  |  | January |  |  | February |  |  | March |  |  | April |  |  | May |  |  |
|----------------------------------------------------------|--------|--|--|-----------|--|--|---------|--|--|----------|--|--|----------|--|--|---------|--|--|----------|--|--|-------|--|--|-------|--|--|-----|--|--|
| Signing contract                                         |        |  |  |           |  |  |         |  |  |          |  |  |          |  |  |         |  |  |          |  |  |       |  |  |       |  |  |     |  |  |
| Development of protocols and interview guides            |        |  |  |           |  |  |         |  |  |          |  |  |          |  |  |         |  |  |          |  |  |       |  |  |       |  |  |     |  |  |
| Request for ethics approval                              |        |  |  |           |  |  |         |  |  |          |  |  |          |  |  |         |  |  |          |  |  |       |  |  |       |  |  |     |  |  |
| Selection of participants for MRA                        |        |  |  |           |  |  |         |  |  |          |  |  |          |  |  |         |  |  |          |  |  |       |  |  |       |  |  |     |  |  |
| MRA data collection in Cabinda                           |        |  |  |           |  |  |         |  |  |          |  |  |          |  |  |         |  |  |          |  |  |       |  |  |       |  |  |     |  |  |
| Transcription of interviews in Cabinda                   |        |  |  |           |  |  |         |  |  |          |  |  |          |  |  |         |  |  |          |  |  |       |  |  |       |  |  |     |  |  |
| Coding and analysis of interview data                    |        |  |  |           |  |  |         |  |  |          |  |  |          |  |  |         |  |  |          |  |  |       |  |  |       |  |  |     |  |  |
| First Draft report for MRA completion                    |        |  |  |           |  |  |         |  |  |          |  |  |          |  |  |         |  |  |          |  |  |       |  |  |       |  |  |     |  |  |
| RDS recruitment of FSW in Cabinda (SADC study)           |        |  |  |           |  |  |         |  |  |          |  |  |          |  |  |         |  |  |          |  |  |       |  |  |       |  |  |     |  |  |
| Data collection for MRA Luanda, Benguela, Bié and Cunene |        |  |  |           |  |  |         |  |  |          |  |  |          |  |  |         |  |  |          |  |  |       |  |  |       |  |  |     |  |  |
| Transcription of interviews                              |        |  |  |           |  |  |         |  |  |          |  |  |          |  |  |         |  |  |          |  |  |       |  |  |       |  |  |     |  |  |
| Coding and analysis of interviews                        |        |  |  |           |  |  |         |  |  |          |  |  |          |  |  |         |  |  |          |  |  |       |  |  |       |  |  |     |  |  |

Programmatic Mapping and HIV/STI Prevalence Study among Key Populations in Angola

| Activity                                | August |  |  | September |  |  | October |  |  | November |  |  | December |  |  | January |  |  | February |  |  | March |  |  | April |  |  | May |  |  |
|-----------------------------------------|--------|--|--|-----------|--|--|---------|--|--|----------|--|--|----------|--|--|---------|--|--|----------|--|--|-------|--|--|-------|--|--|-----|--|--|
| Final MRA report completion             |        |  |  |           |  |  |         |  |  |          |  |  |          |  |  |         |  |  |          |  |  |       |  |  |       |  |  |     |  |  |
| Selection of districts for PM in Luanda |        |  |  |           |  |  |         |  |  |          |  |  |          |  |  |         |  |  |          |  |  |       |  |  |       |  |  |     |  |  |
| Approval of sampling frame              |        |  |  |           |  |  |         |  |  |          |  |  |          |  |  |         |  |  |          |  |  |       |  |  |       |  |  |     |  |  |
| Training of study staff                 |        |  |  |           |  |  |         |  |  |          |  |  |          |  |  |         |  |  |          |  |  |       |  |  |       |  |  |     |  |  |
| Community informant interviews          |        |  |  |           |  |  |         |  |  |          |  |  |          |  |  |         |  |  |          |  |  |       |  |  |       |  |  |     |  |  |
| Data entry and compiling venue lists    |        |  |  |           |  |  |         |  |  |          |  |  |          |  |  |         |  |  |          |  |  |       |  |  |       |  |  |     |  |  |
| Venue informant interviews              |        |  |  |           |  |  |         |  |  |          |  |  |          |  |  |         |  |  |          |  |  |       |  |  |       |  |  |     |  |  |
| Patron and worker interviews            |        |  |  |           |  |  |         |  |  |          |  |  |          |  |  |         |  |  |          |  |  |       |  |  |       |  |  |     |  |  |
| Data cleaning and analysis              |        |  |  |           |  |  |         |  |  |          |  |  |          |  |  |         |  |  |          |  |  |       |  |  |       |  |  |     |  |  |
| Drafting report from PM                 |        |  |  |           |  |  |         |  |  |          |  |  |          |  |  |         |  |  |          |  |  |       |  |  |       |  |  |     |  |  |
| Delivery of draft PM report             |        |  |  |           |  |  |         |  |  |          |  |  |          |  |  |         |  |  |          |  |  |       |  |  |       |  |  |     |  |  |
| Review of report draft and feedback     |        |  |  |           |  |  |         |  |  |          |  |  |          |  |  |         |  |  |          |  |  |       |  |  |       |  |  |     |  |  |
| Dissemination of results                |        |  |  |           |  |  |         |  |  |          |  |  |          |  |  |         |  |  |          |  |  |       |  |  |       |  |  |     |  |  |

MRA: mapping readiness assessment; PM: programmatic mapping

